### 2.7. Randomization and Blinding

We will use a computer-generated number (Epidat 4.2 software, Xunta de Galicia, A Coruña, Spain) to assign each participant to the EG or CG. After completion of baseline assessment (t0), randomization will be applied by an independent researcher not involved in the study. The researcher will communicate in which group the participant has been allocated to the researcher responsible for the program (EG or CG). The researcher in charge of assessments at all time points will be blind to the intervention group. To avoid contamination of the CG and EP, the CG will be unaware of the actions carried out in detail in the EG. In addition, for both groups it will be recorded whether during the course of the study they have received any additional interventions that may influence the outcome variables.

### 2.8. Statistical Analysis

The SPSS 25 software (IBM Statistic Program for the Social Sciences SPSS Statistic, Corp., Armonk, NY, USA) will be used for all data analyses. In all analyses, *p* < 0.05 values will be considered statistically significant. A blind researcher will perform the statistical analysis.

Descriptive statistics will be used to examine the sociodemographic and clinical characteristics of the sample. Data will be expressed as mean ± standard deviation (SD) or means (95% CI) for continuous, and as number or percentages for categorical variables. We will check the normal distribution of variables with the Kolmogorov-Smirnov test and visual inspection. Comparison between the two groups of the study (EG and CG) for baseline demographic data will be done with Student’s *t*-test for continuous, or a Chi-square test for categorical variables. Their non-parametric homologues, i.e., the Mann-Whitney U and Fisher’s exact test, will be used as appropriate.

Bivariate correlations will be used to explore the role of different variables that have been shown to determine cognitive performance in BC patients. Age and educational level will be considered as variables to be controlled for data analysis. Differences in cognitive function of participants receiving vs. not receiving the e-OTCAT program, as well as differences within-groups, will be calculated with a generalized linear mixed model. Substitution by means will be undertaken to treat the possible missing data. All analysis will be “intention-to-treat”. Calculation of the intergroup effect size (using Cohen’s d) will be performed to provide magnitude changes.

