On the other hand, telehealth approaches have become a promising and practiced more frequently among healthcare disciplines [17]. The delivery of remote interventions through digital technology has the potential to reduce economic, time-related and geographical constraints in healthcare systems [18]. Furthermore, telehealth is not a new perspective in cancer patients. Technological support such as web- or telephone-based interventions has been used in cancer rehabilitation, obtaining significant positive outcomes to ameliorate CRCI [19,20,21] and achieve an occupational performance as close as possible to that prior to cancer treatment [22]. This approach includes asynchronous or real-time interventions that might be combined to improve the quality of care. In addition, the current COVID-19 pandemic highlights the need for remote interventions to ensure supportive care for at-risk populations such as cancer patients [23].

We propose the e-OTCAT program, taking up the recommendation of a recent meta-analysis suggesting the testing of the effectiveness of interventions targeted to cognitive impairment in a preventive setting for BC patients scheduled for neurotoxic chemotherapy [24], as well as the potential of occupational therapy and the advantages of a telehealth approach. It will involve a telehealth cognitive-adaptive training to prevent CRCI in women with BC undergoing neurotoxic chemotherapy. The e-OTCAT program has been created to work in combination with the effects of cognitive training to enhance brain plasticity and to address other co-existing factors during this period such as psychological distress and fatigue, as well as occupational performance and quality of life.

We hypothesize that women with BC performing the e-OTCAT program simultaneously to the first course of chemotherapy will report less CRCI, better quality of life with other clinical variables, and better occupational performance than those receiving the usual care.

The main objective will be to study the preventive effects of the e-OTCAT program on CRCI, comparing the differences on the cognitive function between two groups of women with BC undergoing chemotherapy: the experimental group (EG) performing the e-OTCAT program for 12 weeks, starting at the same time as they begin the first course of chemotherapy, and the control group (CG) receiving the usual care.

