Secondary objectives will be to investigate the immediate and medium-term effects of the e-OTCAT program on cognitive function, psychological distress, fatigue, sleep quality, quality of life and occupational performance in women with BC undergoing chemotherapy.

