### 2.4. Outcome Measures

#### 2.4.1. Primary Outcome

##### Cognitive Function

The Functional Assessment of Cancer Therapy-Cognitive Function (FACT-Cog) version 3 [27] will be used to assess subjective cognitive function. The FACT-Cog comprises 37 questions to be scored from 0 (“never” or “nothing” to 4 “several times a day” or “very much”), and grouped into four subscales: perceived cognitive impairment, perceived cognitive abilities, impact of perceived cognitive impairment on QoL and comments from others about cognitive performance. Higher scores indicate better cognitive function. Cronbach’s α values for BC patients range from 0.71 to 0.93 [28]. The Spanish version of the scale will be used.

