### 2.6. Sample Size

The sample size for cognitive function was calculated based on a similar previous study using FACT-Cog version 3.0 [43]. Assuming an alpha error of 0.05, a power of 85% and a medium effect size (d = 0.58) based on the results of the reference study, we need a sample of 44 participants for each group (G*Power v.3.1). In order to compensate for a possible 10% dropout rate [44], we will recruit a total of 98 participants (49 per group).

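### The primary FACT-Cog test is not pinned to one score, visit and contrast, while p < 0.05 applies to every analysis and the sample size assumes one comparison

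*Protocol article*

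**What the plan says.** - **Main objective (1. Introduction).** It is to study prevention of cognitive impairment by "comparing the differences on the cognitive function between two groups of women with BC undergoing chemotherapy". No score or visit is attached.
- **Secondary objectives (1. Introduction).** "Secondary objectives will be to investigate the immediate and medium-term effects of the e-OTCAT program on cognitive function", followed by distress, fatigue, sleep, quality of life and occupational performance.
- **Visits (2.3. Procedure).** Baseline (t0), 12 weeks (t1) and six months (t2) after randomization. Neither follow-up is called primary.
- **Primary outcome (2.4.1).** FACT-Cog version 3, with its items "grouped into four subscales: perceived cognitive impairment, perceived cognitive abilities, impact of perceived cognitive impairment on QoL and comments from others". Neither a total nor a subscale is singled out.
- **Secondary outcomes (2.4.2).** These open with the TMT and two WAIS-IV indexes, under a heading for other cognitive measures.
- **Sample size (2.6).** "The sample size for cognitive function was calculated based on a similar previous study using FACT-Cog version 3.0". The inputs are: "Assuming an alpha error of 0.05, a power of 85% and a medium effect size (d = 0.58) based on the results of the reference study". The result is 44 per group, raised to 49 per group (98 in total) for 10% dropout. The score and visit behind d are not given, nor is the sidedness of alpha.
- **Analysis (2.8).** Between-group and within-group differences in cognitive function come from a generalized linear mixed model. "In all analyses, *p* < 0.05 values will be considered statistically significant".

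**The concern.** A primary analysis is defined by a score, a visit and a contrast. Here only the instrument and the model family are fixed. With two follow-ups and one flat threshold, a reader of the eventual report could not tell whether a significant FACT-Cog result at one visit was the planned test or the better of two. The 5% error rate and the power in section 2.6 belong to a single comparison and do not carry over to a choice among several.

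The wording of the objectives adds to this. The only follow-ups are at 12 weeks and six months, so the immediate and medium-term effects on cognitive function take up both available visits. Unless the secondary objective is limited to the objective tests, it claims the same contrasts as the main objective.

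The exposure matters more in this trial than in most. The outcome is self-reported by unblinded participants, and the Discussion acknowledges expectation bias. The 0.05 rule also covers within-group differences, although the main objective is a comparison between groups.

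**Working it through.** **1. The plan's own figure.** Inputs from 2.6: d = 0.58, alpha 0.05, power 0.85, 1:1 allocation. The normal approximation is n per group = 2(z_alpha + z_power)² / d².

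- One-sided: 2(1.645 + 1.036)² / 0.3364 = 42.7, so 43. The t-test version gives 43.4, so **44**, which matches the plan.
- Two-sided: 2(1.960 + 1.036)² / 0.3364 = 53.4, so 54. The t-test version gives 54.4, so **55**, which does not match.
- Dropout: 44 / 0.9 = 48.9, so 49 per group and 98 in total, which matches.

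The stated size therefore fits one comparison at one-sided 0.05. With 44 per group the t-test power is 85.4% one-sided and 76.7% two-sided.

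**2. One score, either visit.** For k independent two-sided tests at 0.05, the chance of at least one false positive is 1 − 0.95^k. In the programme's favour alone it is 1 − 0.975^k. The documents give no correlations, so those below are assumptions, evaluated by simulation of correlated z-tests.

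| Between-visit correlation | Any direction | Favouring the programme |
|---|---|---|
| 0 | 1 − 0.95² = 9.8% | 1 − 0.975² = 4.9% |
| 0.5 | about 9% | about 4.6% |
| 0.7 | about 8.3% | about 4.2% |
| 0.8 | about 7.9% | about 3.9% |

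The nominal values are 5% and 2.5%. If the tests were one-sided at 0.05, as the sample size implies, the favourable error for two independent tests would be 1 − 0.95² = 9.8% against a nominal 5%.

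**3. Any of four subscales, either visit (4 × 2 = 8 tests).**

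| Correlation between subscales / between visits | Any direction | Favouring the programme |
|---|---|---|
| 0 / 0 | 1 − 0.95⁸ = 33.7% | 1 − 0.975⁸ = 18.3% |
| 0.3 / 0.5 | about 30% | about 15% |
| 0.7 / 0.7 | about 21% | about 10.5% |

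The independent case is an upper illustration, since subscales and repeated measures on the same women are correlated.

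**4. Splitting alpha instead of naming one visit.** Bonferroni at 0.025 per visit needs 55 evaluable women per group one-sided, or 66 two-sided. Naming one visit leaves the calculation in 2.6 unchanged on its one-sided basis.

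**The case against.** **Only a condensed article is shown.** Score, visit, contrast and testing order may be set out in a full protocol or analysis plan, and silence alone would not be a finding. That is fair as far as it goes. But the article is not silent: it fixes one threshold for all analyses, and it puts cognitive function in both tiers of objectives. A later document that named a single test would have to narrow both statements.

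**The overlap may be loose wording.** A reader might infer that every FACT-Cog contrast has been labelled secondary. The text does not go that far. The secondary objective does not mention the FACT-Cog, section 2.4.2 lists the TMT and WAIS-IV as secondary, and the Discussion repeats that split. The primary instrument is fixed; the ambiguity lies in the objectives.

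**No rule says that any subscale decides success.** This stands. Section 2.4.1 describes the structure of the instrument, and 2.6 uses one effect size. The eight-test figures are conditional. It is also tempting to count every secondary scale component at both visits, but no statement says that all will be tested or will decide anything, and unadjusted secondary tests are not in themselves an error.

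**Two-sided error overstates the harm.** About half of the false positives would favour control, so the favourable-direction figures are the relevant ones for a false claim of benefit.

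**Within-group tests.** A reader might infer that equal decline in both arms would often look like prevention, significant in controls only. With a decline of 0.3 SD and 44 per group, paired power is 0.494, so this happens in 0.494 × 0.506 = 25% of trials. But 25% is the maximum of p(1 − p). At 0.1 or 0.5 SD it is about 9%. The main objective is between groups, so nothing says that such a pattern would count as success.

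**Conclusion.** The concern holds in a limited form. The FACT-Cog is clearly primary, but its decisive score, visit and contrast are not named. The flat 0.05 rule is wider than the single comparison that the trial was sized for. The secondary objective overlaps the main one unless it is confined to the objective tests.

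On the most charitable reading, one score tested at either visit, the two-sided error is 8-10% (4-5% favourable against 2.5%). That inflation is real but modest. If any of four subscales counted, it would be 21-34% (10-18% favourable). These ranges rest on assumed correlations of 0 to 0.8 between visits in the first case. In the second they run from independence to 0.7 between subscales and between visits.

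The documents do not support saying that success will be claimed on any subscale, or that the plan contains no primary outcome.

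**What to change.** Before any unblinded analysis:

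1. Name as the sole primary test at 0.05 the between-group contrast from the mixed model, on one FACT-Cog score (the one behind d = 0.58) at one visit, for example t1, the end of the programme.
2. Test t2 on the same score only if the primary test is significant, or label it secondary.
3. Reword the secondary objective so that it does not repeat the primary contrast, for instance by naming the TMT and WAIS-IV and the remaining visit.
4. Limit the p < 0.05 rule to the primary test (and t2, if it is ordered after it). Present the other subscales and scales as supportive, with 95% confidence intervals. Base no efficacy claim on within-group tests.
5. State sidedness. If the test is two-sided, restate the power as about 77% for 44 evaluable per group, or provide 55 evaluable per group for 85% (55 / 0.9 = 61.1, so 62 per group recruited, 124 in total).

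**Cost.** Items 1 to 4 change wording only and need no more participants, but fewer results can be called significant. Item 5 makes the stated power less favourable, or the trial larger, if the test is two-sided. Sharing alpha across the two visits instead would raise the evaluable number to 55 (one-sided) or 66 (two-sided) per group.

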### 2.2. Participants

Participants will be recruited from the University Hospital of San Cecilio and the University Hospital of Virgen de las Nieves (Granada, Spain), referred by the oncologists and nurses in charge. Eligible women with BC scheduled to receive chemotherapy will be recruited if they meet the inclusion criteria as follows: (a) female BC who are going to start adjuvant or neoadjuvant chemotherapy, (b) stage I-III of BC, (c) age range 18–70 years old, (e) must be able to speak, read and write Spanish well to complete written and verbal assessment, neurocognitive tests and study sessions, and (f) must have basic phone skills. Women will be excluded if they have: (a) a history of cognitive, mental and/or physical disorder that may make participation in the study difficult, the completion of assessments and the performance of intervention i.e., Alzheimer disease, Parkinson’s disease, multiple sclerosis, schizophrenia, bipolar disorder, etc.); (b) a prior history of cancer or secondary diagnosis of cancer, (c) a prior history of chemotherapy, or (d) hearing or visual deficit.

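### The mixed model names age and education as controls but does not adjust for baseline FACT-Cog or hold the group means equal at t0, so the treatment contrast may be a less precise difference of changes.

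*Protocol article*

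**What the plan says.** All statements are in the protocol article.

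- **Covariates (section 2.8):** "Age and educational level will be considered as variables to be controlled for data analysis". The sentence just before it reads in part "Bivariate correlations will be used to explore the role of different variables".
- **Model (section 2.8):** a generalized linear mixed model is to give both the difference between arms and the differences within each arm. How the t0 score enters that model is not stated.
- **Timing (sections 2.3 and 2.7):** assessments are at t0, at 12 weeks (t1) and at six months (t2). Allocation takes place once the t0 assessment is complete.
- **Primary outcome (section 2.4.1):** FACT-Cog version 3.
- **Sample size (section 2.6):** alpha 0.05, power 85% and a "medium effect size (d = 0.58) based on the results of the reference study", from which "we need a sample of 44 participants for each group (G*Power v.3.1"). The section does not say whether the test is one- or two-sided, or on which SD the 0.58 is standardised.

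**The concern.** The article does make a covariate choice, and the choice leaves out the variable that is usually the best predictor of a follow-up questionnaire score: the same questionnaire before treatment. Because FACT-Cog is taken before allocation, it is a legitimate covariate that costs nothing to collect.

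Within-group differences need the t0 score, so t0 is probably in the model as one of three repeated responses. The usual default form of such a model gives each arm its own mean at every visit, t0 included. The treatment effect is then the group-by-time contrast, which is the difference between arms in change from baseline. That contrast treats the t0 difference between arms as something to be estimated, when randomisation makes its expected value zero. The price is precision in a trial of 98 women.

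**Working it through.** **Inputs.** From section 2.6: 44 evaluable per group, d = 0.58, alpha 0.05, target power 85%, 10% dropout. Assumed, because the article does not give them: the correlation r between t0 and follow-up FACT-Cog, equal SDs at the two visits, and d = 0.58 standardised on the raw-score SD.

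**Step 1: reproduce the stated sample size** (two-sample t-test, noncentral t).
- One-sided 5%: 44 per group are needed, and power at 44 is 85.4%. Then 44/0.9 = 48.9, so 49 per group and 98 in total. This matches the article.
- Two-sided 5%: 55 per group are needed, and power at 44 is 76.7%. This does not match.

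Both readings are therefore carried forward.

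**Step 2: variance of the two contrasts.** With outcome variance σ² at each visit, the per-woman variance is
- difference of changes: 2σ²(1 − r)
- baseline-adjusted: σ²(1 − r²)

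The ratio is 2(1 − r)/[(1 − r)(1 + r)] = 2/(1 + r). At r = 0.3 it is 2/1.3 = 1.54, and at r = 0.5 it is 2/1.5 = 1.33. It is above 1 for every r below 1, and it depends on neither d nor sidedness.

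**Step 3: power at 44 per group.** The effective standardised effects are
- change contrast: 0.58/√(2(1 − r))
- baseline-adjusted: 0.58/√(1 − r²)

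For example, at r = 0.3 these are 0.58/√1.4 = 0.490 and 0.58/√0.91 = 0.608. The noncentral t (86 degrees of freedom, or 85 with the covariate) gives:

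| r | Two-sided: change | Two-sided: adjusted | One-sided: change | One-sided: adjusted |
|---|---|---|---|---|
| 0.3 | 62.3% | 80.5% | 73.8% | 88.2% |
| 0.4 | 69.0% | 83.5% | 79.4% | 90.3% |
| 0.5 | 76.7% | 87.4% | 85.4% | 92.9% |
| 0.6 | 85.3% | 92.0% | 91.5% | 95.8% |

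Ignoring baseline altogether gives 76.7% (two-sided) or 85.4% (one-sided) at every r. The change contrast falls below that when r is under 0.5 and equals it at r = 0.5.

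**Step 4: where 85% is reached on a two-sided test.** The adjusted contrast gets there at r of about 0.44, and the change contrast at about 0.60.

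The table compares the arms at one follow-up visit. It leaves out any variance explained by age and education, and any contribution from the other follow-up visit.

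**The case against.** **The article does not exclude baseline.** It does not say that age and education are the only controls, and a mixed model holding t0 with a common mean across arms would be about as efficient as covariate adjustment. A condensed article may also leave model terms to a fuller document. This stands in part: the text cannot be read as rejecting baseline adjustment. But section 2.8 does go as far as naming covariates, and as written the list leaves this one out while nothing else secures the equivalent constraint.

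**A reader might infer that the trial is short of power and that adjustment would restore it.** The article does not support that as a plain statement. Section 2.6 gives no sidedness; on the one-sided reading that reproduces 44 per group there is no shortfall, and on a two-sided test adjustment reaches 85% only if r is about 0.44 or more. Sidedness is a separate question. What survives on either reading is that at r = 0.3 or 0.4 a change contrast falls below 85%.

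**The absolute powers rest on the scale of d.** This is right. If 0.58 is already a change-score effect, the change contrast has 76.7% two-sided power at every r; if it is an adjusted effect, the gain from adjustment is already counted. The ordering and the ratio 2/(1 + r) do not change.

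**The t-test comparator is not the planned model.** Also right: age and education may remove some variance that overlaps with baseline FACT-Cog, so gains measured from 76.7% may be overstated. For this reason the comparison that matters is change against adjusted.

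**Two further inferences are tempting.** One is that chemotherapy setting and hospital must also be in the model. Section 2.2 admits women "female BC who are going to start adjuvant or neoadjuvant chemotherapy" from two hospitals, but the article gives no figure linking either factor to FACT-Cog and describes no stratification by them. Under an assumed extra R² of 1% to 5%, setting would move two-sided power only from 76.7% to between 77.1% and 78.8%. The other is that the bivariate correlations will select covariates after outcomes are seen. The article describes them as exploratory and names age and education in advance; nothing says they feed the model.

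**Conclusion.** The point holds as a gap in how section 2.8 sets out the model. The baseline score of the primary outcome is available before randomisation, yet the named controls omit it and nothing constrains the arms to a common t0 mean. If t0 is fitted as an ordinary repeated outcome with a free group effect, which is likely but not stated, the treatment contrast has 1.54 times the variance of an adjusted one at r = 0.3 and 1.33 times at r = 0.5. In power terms that is about 18 and 11 percentage points on a two-sided test (80.5 − 62.3 and 87.4 − 76.7), and about 14 and 8 on a one-sided test (88.2 − 73.8 and 92.9 − 85.4).

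The ratio rests on the assumed r and on equal SDs at the two visits. The powers rest also on d = 0.58 being a raw-score effect. The treatment estimate is not biased by the choice; what is lost is precision.

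**What to change.** In section 2.8, fix one of two equivalent forms of the primary model before outcome data are seen:

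1. Model FACT-Cog at t1 and t2, with group, visit and group × visit, adjusting for baseline FACT-Cog and baseline × visit alongside age and educational level, and allowing for the correlation within each participant.
2. Keep t0 as a third outcome but constrain the group means to be equal at t0. This form also yields the planned within-group differences directly.

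Apply the same form to each secondary outcome with its own baseline value.

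The cost is analysis wording and one or two degrees of freedom. Recruitment, visits and data collection are unchanged.

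### Filling missed assessments with an unspecified mean would either understate standard errors or shrink the treatment effect, and the planned mixed model does not need it

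*Protocol article*

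**What the plan says.** Section 2.8 gives one rule for missing data: "Substitution by means will be undertaken to treat the possible missing data". The sentence before it says that differences between and within groups "will be calculated with a generalized linear mixed model". The sentence after it declares every analysis intention-to-treat, and the section then promises an intergroup Cohen's d. The type of mean (arm, overall, or the woman's own) is not given. Nor does the text say whether the rule covers whole missed visits or single items.

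Section 2.6 sets the expected loss. It sizes the trial at 44 per group for d = 0.58 and raises this to 49 per group, 98 in all, "In order to compensate for a possible 10% dropout rate". Section 2.3 places assessments at baseline, 12 weeks and six months. The primary outcome (section 2.4.1) is the FACT-Cog, a questionnaire of 37 items.

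**The concern.** Single mean substitution treats invented values as observed ones. A filled value adds no spread but is counted as a participant, and it carries nothing of that woman's own baseline. The within-person correlation that a mixed model relies on is therefore weakened. The primary p-value, confidence interval and effect size could all be affected.

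The step is also unnecessary. A likelihood-based mixed model uses every observed visit and is valid when loss is missing at random.

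Loss may also differ between the arms. Only the experimental arm has two videoconference sessions a week for 12 weeks plus homework during chemotherapy (section 2.5), and the Discussion names adherence bias as a limitation.

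**Working it through.** **Inputs from the article.** d = 0.58, alpha 0.05, power 85%, 44 evaluable per arm, 10% dropout, 49 per arm (section 2.6); three assessments (section 2.3).

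**Assumptions, not in the article.** SD 1; within-person correlation 0.5 (0.7 as a check); a shared decline of 0.5 SD; dropouts miss both follow-ups; a two-sided 5% test at 12 weeks; loss of 20% as a second case.

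**The plan's own figures.** 44 / 0.9 = 48.9, so 49 per arm and 98 in total, as stated. The 44 reproduces with a one-sided t-test at 0.05. A two-sided test needs 55 per arm, and 44 gives 77% power. That is a separate matter from this one.

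**Arm-mean fill, closed form.** Let f be the missing fraction and n = 49.
- True standard error of the arm difference: √(2 / (n(1 − f))). At f = 0.10 this is √(2/44.1) = 0.213.
- Reported standard error after filling: the variance shrinks to about (1 − f) and is divided by n, giving √(2(1 − f)/n) = √(1.8/49) = 0.192.
- Ratio: 1 − f = 0.90.
- Actual type I error: 2(1 − Φ(1.96(1 − f))). At f = 0.10 this is 2(1 − Φ(1.764)) = 7.8%. At f = 0.20 it is 2(1 − Φ(1.568)) = 11.7%.

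**Overall-mean fill, closed form.** A fraction f in each arm receives the same value, so the expected difference is d(1 − f): 0.58 × 0.9 = 0.52 and 0.58 × 0.8 = 0.46.

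**Simulation.** 6,000 trials per setting, 49 per arm, loss random and equal in both arms, correlation 0.5:

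| Handling | Model | Type I error, 10% loss | Type I error, 20% loss | Mean estimate when d = 0.58 (10%, 20%) |
|---|---|---|---|---|
| Arm mean | Random-intercept mixed model | 6.5% | 9.1% | 0.58, 0.58 |
| Arm mean | ANCOVA | 7.5% | 11.0% | 0.58, 0.58 |
| Overall mean | Random-intercept mixed model | 5.1% | 5.9% | 0.52, 0.46 |
| Overall mean | ANCOVA | 4.6% | 4.5% | 0.52, 0.46 |
| No fill | Baseline-adjusted, observed data | 4.6% | 4.4% | 0.58, 0.58 |

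With correlation 0.7, the arm-mean fill gives 7.2% and 9.1% (mixed model) and 8.0% and 11.9% (ANCOVA). Filling with the woman's own baseline value keeps about 5% error at 10% loss, but also shrinks the estimate to 0.52.

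**Power with the overall-mean fill.** The mixed model has 74% power at 10% loss and 64% at 20%. These should not be set against the 88% and 83% of the baseline-adjusted analysis, which is more efficient in itself. Like for like:
- Change score. At correlation 0.5 the SD of change is √(2(1 − 0.5)) = 1, so 44 observed women per arm have the 77% power given above. The filled change-score test has 72%.
- ANCOVA. Power falls from 88% to 87% at 10% loss and from 83% to 80% at 20%.

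**Cohen's d.** If d is standardised by the SD of arm-mean-filled data, it is inflated by 1/√0.9 = 1.054 at 10% loss and 1/√0.8 = 1.118 at 20%.

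**Assumed differential loss, no true effect.** Suppose that experimental-arm dropouts all have below-average baseline scores. With 20% against 10% loss, the bias is +0.10 SD (arm mean) or +0.08 SD (overall mean), and mixed-model type I error is 10.7% or 7.6%. With 10% loss in each arm, type I error is 7.8% or 6.4%. A weaker link between loss and baseline, again with 20% against 10%, gives +0.045 SD for the arm mean. Across the differential-loss settings the observed-data, baseline-adjusted analysis stays at 4.9–5.3%.

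**The case against.** A reader might infer that the plan raises the false-positive rate whatever is done. The article does not support that, because it does not name the mean. With an overall-mean or own-value fill and equal random loss, error stays near 5% and the harm is attenuation. Inflation needs an arm-mean fill, or loss that differs by arm and relates to baseline.

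It is also tempting to give 8% and 12% as the size of the problem. Those are the closed-form and ANCOVA figures, whereas the plan names a mixed model, for which the inflation is smaller. The 20% loss appears nowhere in the article, and at the planned 10% the inflation is modest. If loss at 12 weeks were only 5% (assumed), the formula gives 2(1 − Φ(1.862)) = 6.3%.

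Three further limits stand:
- The article gives no arm-specific loss, so the differential scenario shows what could happen and is not an estimate for this trial.
- The inflation of Cohen's d arises only if the SD comes from filled data, which the article does not say.
- The observed-data analysis performs well here partly because the simulated loss depends on nothing beyond baseline. If loss depends on unseen follow-up scores, the mixed model is biased too.

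Finally, the rule might mean only single missing items within a questionnaire, in which case none of these figures apply. That reading is possible but less natural for a sentence placed between the mixed model and the intention-to-treat statement.

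None of this rescues the rule for missed visits. It is a stated method and not a detail left to an analysis plan, and nothing else in the article softens it.

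**Conclusion.** The concern holds in conditional form. If missed assessments are filled, an arm-mean fill understates the standard error and gives about 6.5–8% type I error at the planned 10% loss, and about 9–12% at an assumed 20%. An overall-mean fill holds about 5% under equal random loss, but shrinks 0.58 to about 0.52 (0.46 at 20%) with some loss of power. Both can be biased towards benefit under arm-differential loss related to baseline.

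The direction of each effect follows from the method itself. The sizes rest on the assumed correlation, loss rates and dropout patterns. The effect at the planned loss is moderate, but it falls on the primary result and is easily avoided.

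**What to change.** Delete the substitution sentence. State instead that all randomised women are analysed in their allocated group with the likelihood-based mixed model fitted to all observed visits, and that no outcome is filled with a mean. Compute Cohen's d with an SD from observed data. Keep person-mean prorating only for isolated missing items within a completed questionnaire, and say so.

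Because missing at random may fail, add a sensitivity analysis, for example multiple imputation with a shift to worse scores for women who drop out. Its exact form can be left to the analysis plan.

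The cost is a change of wording, a little more analysis work, and slightly wider confidence intervals that reflect the information actually collected.
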